### **8.2.2.1 Humoral Assays**

Ten mL of blood will be collected per draw for humoral assays at 6 time points: 1) day 0 prior to the 1st vaccination, 2) just prior to the 2nd vaccination, 3) 28 days after the 2nd vaccination, 4) just prior to the 3rd vaccination, and 5) 28 days after the 3rd vaccination, 6) 56 days after 3rd vaccination. The assays to be performed include an ELISA to determine antibody titers against the circumsporozoite antigen and an Adenovirus Neutralization Assay for neutralizing antibody titers against Adenovirus type 35, and possibly other relevant Adenovirus serotypes (e.g. Adenovirus type 5).

### **8.2.2.2 Cellular Assays**

Blood draws for assessment of cellular immune response will be performed at six time points: 1) day 0 prior to the 1st vaccination, 2) just prior to the 2nd vaccination, 3) 28 days after the 2nd vaccination, 4) just prior to the 3rd vaccination, and 5) 28 days after the 3rd vaccination, 6) 56 days after 3rd vaccination. Per blood draw, 40 mL of blood will be used for cellular assays, of which 30 mL is used for PBMC isolation and 10 mL for whole blood stimulation followed by cytokine ELISA. Blood volumes were determined to ensure sufficient numbers of cells to establish stimulation protocols and evaluate cell-mediated immune responses. Cellular assays will be performed when the first 6 samples have been collected with samples randomized over assay runs to distribute variation over all groups and timepoints.

---

 For description of the Adenovirus Neutralization Assay, see Sprangers, MC et al. Quantifying Adenovirus Neutralizing Antibodies by Luciferase Transgene Detection: addressing preexisting immunity to vaccine and gene therapy vectors. J. Clin. Microbiol. 41(11):5046, 2003.

Although T cell responses are optimally examined using freshly isolated cells, examining fresh samples collected at different time points is not possible. It has been shown that both CD4+ and CD8+ T cells are readily detected in frozen samples. Thus, Elispot and Intracellular Cytokine Staining (ICS) will be performed on cryopreserved peripheral blood mononuclear cells. Characterization of antigen-specific T cell responses will be evaluated based on the quantity and the phenotype of responding cells to a specific antigenic stimulus using an Elispot assay as the primary quantitative readout and an IFN- $\gamma$  ICS assay to preliminarily assess the CD4+ vs. CD8+ T cell response. The ICS assay will include the phenotypic markers CD4, CD8, and CD3 and intracellular detection of IFN- $\gamma$ . Additional markers may be included as feasible. In addition whole blood assay will also be used to measure secreted cytokines production (IFN- $\gamma$  and IL10) in culture supernatant.

Stimulation of cells in the Elispot, ICS, and whole blood assays will utilize an overlapping peptide matrix. A pool of 15-mer peptides was acquired which overlap by 11 amino acids spanning the entire length and corresponding to the amino acid sequence of the circumsporozoite protein used in the vaccine.

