### 5.1 Selection of the study population

From the up to date database of the population in the study area, a list of all adults 18-45 years old from the village of Balonghin and neighbour villages will be drawn. Subjects will be visited at home by field workers who will explain the study to them. They will then be invited to the vaccinology unit based at Balonghin village to receive more information about the study. An educational process will be instituted which will represent several levels of authority starting from the civil authorities to the local village leadership and down to small groups and ultimately individual. Those who provide a signed informed consent will be screened for study eligibility. A total of 48 eligible adults will be enrolled.

In order to establish a bank of PBMC from individuals with known responsiveness against malaria, for use as positive standards in future human cellular assays in studies with malaria vaccine candidates, the informed consent will include a statement that subjects may be approached for an additional blood sampling outside this vaccine trial.

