### 5.2 Enrollment Within Each Dosage Cohort

This study will be performed as a randomized, double-blinded, dosage-escalation study. The first dosage cohort consists of 12 subjects: 10 will receive the Ad35.CS.01 malaria vaccine while 2 will receive placebo control product. The subjects in the first cohort will be enrolled as follows: subject #1 followed by subject #2 with a minimum of a 30 minute waiting period between vaccinating subjects. This schedule will allow for assessment of immediate reactions of subject #1 prior to vaccinating subject #2. Following enrollment of subject #2, a minimum of a 2-day waiting period will be required prior to enrollment of the next four subjects. This schedule will allow for further reactogenicity assessment. The minimum 2-day waiting period will continue between each group of four subjects until the enrollment of 12 subjects into the first cohort has been met.

Following the SMC review of 14-day safety data of the first cohort, the second dosage cohort will contain 12 subjects (10 will receive Ad35.CS.01 and 2 will receive normal saline placebo control product). Six subjects will be enrolled, followed by a minimum of a 2-day waiting period before the next six subjects will be enrolled. The minimum 2 day waiting period will continue between each group of six subjects until the enrollment of 12 subjects into the second cohort has been met. This process will be repeated for the third and fourth cohorts.

Enrollment of additional subjects within any dosage cohort will not occur if a halting rule is met. Enrolled subjects who drop out of the study for any reason will not be replaced.

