## **8.2.2 Humoral and Cell-mediated Immune Assays**

To assess both humoral and cell-mediated immune responses to the vaccine, 50 mL of blood will be drawn from subjects on the following study days: 0, 28, 56, 84, 112, 140 days. From the 50 mL blood for immunological responses, 10mL will be used for serum isolation and subsequent humoral assays, and 40 mL blood will be used for cellular assays: 30mLs for PBMC isolation and 10 mL for whole blood stimulation followed by cytokine ELISA. Complete information on all immunological assays, including methods, reference standards, and performance sites are included in the Manual of Procedures.

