**Specimen Shipment**

For analysis of the humoral response, two serum aliquots of each blood draw will be shipped to Crucell BV, Leiden, Netherlands and pending shipment failure, the remainder of the specimens will be stored at CNRFP. If additional storage is necessary, specimens may be shipped to Fishers Repository. For analysis of the cellular immune response, PBMC specimens will be shipped to Crucell BV, Leiden, Netherlands in two separate shipments. Whole blood assays will be processed at CNRFP/PDVAP laboratory in Ouagadougou, Burkina Faso.

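### The start rule for cellular assays does not define its 6 samples; on two of three readings, early runs cannot contain all dosage groups and timepoints

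*Protocol*

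**What the plan says.** Section 8.2.2.2 opens with "Blood draws for assessment of cellular immune response will be performed at six time points" and numbers them one to six. Section 8.2.2 gives the days: "0, 28, 56, 84, 112, 140 days". The paragraph in 8.2.2.2 ends by saying that the assays are "performed when the first 6 samples have been collected with samples randomized over assay runs to distribute variation over all groups and timepoints". The sentence therefore holds a timing condition and a purpose.

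The same section gives the reason for using frozen cells: "examining fresh samples collected at different time points is not possible". Elispot and ICS are done on cryopreserved PBMC. Section 8.2.3 (Specimen Shipment) says "PBMC specimens will be shipped to Crucell BV, Leiden, Netherlands in two separate shipments", without saying when each leaves or what it contains. The whole blood assay is separate: "Whole blood assays will be processed at CNRFP/PDVAP laboratory in Ouagadougou, Burkina Faso".

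Enrolment is sequential. Section 5.2: "Following the SMC review of 14-day safety data of the first cohort, the second dosage cohort will contain 12 subjects", and the process repeats for the third and fourth cohorts. Section 15.4 starts the 14 days only once everyone in a cohort has had the first dose. Section 11.2 places the primary analysis after Day 140 of the last cohort.

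**The concern.** Randomising samples over assay runs protects a comparison across dosages only if the samples to be compared are in the freezer when the runs are drawn up. A start condition met early in a sequential dose escalation works against that. The lowest dosage is sampled first, and the samples taken after the third dose at the highest dosages come last.

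If early runs lack those samples, a shift between runs (reagent lot, operator, thaw batch) falls partly along dosage group and timepoint. With 10 vaccine recipients per group, little could be recovered afterwards by adjustment. What is at stake is the description of T-cell response by dosage. Sections 3.2.3 and 11.1 list it as exploratory, while section 3.1 and the Protocol Summary also place it under the secondary objective.

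**Working it through.** The plan gives no figure of its own to reproduce here. The check is a calendar of which samples exist when the condition is met.

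**Inputs**
- Subjects: "A total of 48 eligible adults will be enrolled" (section 5.1), in four groups of 12 (section 4). Planned samples: 48 × 6 = 288.
- Group A staging (section 5.2): 2, then 4, 4 and the last 2, at least 2 days apart, so first doses on study days 0, 2, 4 and 6.
- Groups B to D (section 5.2): 6 + 6, at least 2 days apart.
- Escalation: 14 days after the cohort's last first dose (section 15.4), plus a safety review time L. The protocol does not state L, so it is assumed at 0, 14 and 30 days.
- Sample days are nominal; visit windows are ignored. Study day 0 is the first Group A dose.

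**First-dose days**
Start of next cohort = last first dose of prior cohort + 14 + L.
- L = 0: B starts 6 + 14 = 20 (ends 22); C 22 + 14 = 36 (ends 38); D 38 + 14 = 52 (ends 54).
- L = 14: B 34–36, C 64–66, D 94–96.
- L = 30: B 50–52, C 96–98, D 142–144.

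**Reading 1: six tubes.** Two Group A subjects are sampled on day 0 and four on day 2. These six are all Group A, Day 0. The first Group D sample comes no earlier than day 52, when 60 samples from A to C already exist (A 24, B 24, C 12).

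**Reading 2: the six timepoints of the first subject to finish.** The condition is met on study day 0 + 140 = 140. Samples in store on that day:

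| L | A | B | C | D | Total of 288 |
|---|---|---|---|---|---|
| 0 | 62 | 60 | 48 | 48 | 218 |
| 14 | 62 | 48 | 36 | 24 | 170 |
| 30 | 62 | 48 | 24 | 0 | 134 |

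For example, at L = 0 Group A has 12 × 5 + 2 = 62, since only the two day-0 subjects have reached Day 140. Group B has 12 × 5 = 60 (Day 112 falls on 132–134). Group C has 12 × 4 = 48 and Group D 12 × 4 = 48 (its Day 84 falls on 136–138).

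Only Days 112 and 140 follow the third dose, because the Day 84 sample is taken before it. Of the 48 × 2 = 96 planned samples after the third dose, those in store on day 140 are:
- L = 0: A 12 + 2 = 14, B 12, C 0, D 0; 26 in all. Group C's Day 112 starts on 36 + 112 = 148 and Group D's on 52 + 112 = 164.
- L = 14: A 14, the others 0 (Group B's Day 112 starts on 34 + 112 = 146). Group D has only Days 0 and 28.
- L = 30: A 14, the others 0. Group D has no sample at all.

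**Reading 3: all six timepoints of all subjects.** The condition is met at the last Group D Day 140: 54 + 140 = 194 (L = 0), 96 + 140 = 236 (L = 14) or 144 + 140 = 284 (L = 30). All 288 samples are then available and the randomisation can be done as described.

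**The case against.** The best case for the protocol is that Reading 3 is what was meant. The sentence closes a paragraph that lists exactly six timepoints, so the number 6 most naturally refers to those. Freezing cells because fresh testing across timepoints cannot be done is an argument for batch testing. Two shipments are hard to square with starting at six tubes. A primary analysis after Day 140 of the last cohort needs no early cellular results. No section assigns runs by cohort, and the sentence itself asks for randomisation. Section 8.2.2 also sends assay details to the Manual of Procedures, which is not shown and may settle run layout. The outcomes are exploratory in a descriptive study, and no safety or escalation decision rests on them.

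Most of this stands, and it limits the point. A reader might infer that the timing condition makes randomisation impossible, that assay run is aliased with dosage group, or that all 288 samples are compromised. The documents do not support that. Under Reading 3 nothing is affected. Under Reading 2 with no review time, all four groups could share runs and the confounding would be partial.

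The objection does not show that the text says Reading 3. A subject has only six scheduled draws, so speaking of the first 6 fits poorly with waiting for everyone's sixth. A condition fixed in the protocol should not depend on an unseen manual for its meaning. The shipment text leaves a further gap: a split by calendar time would recreate the problem if the first shipment were tested on arrival.

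**Conclusion.** The point holds as a badly defined timing rule. Two of its three readings defeat the purpose stated in the same sentence; the third does not, and the text does not say it. On the six-tube reading, the first run would hold one group and one timepoint. On the first-finisher reading, 218, 170 or 134 of 288 samples exist at review times of 0, 14 or 30 days, and in none of these cases do Groups C and D have a sample from after the third dose.

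These counts rest on the fastest enrolment that section 5.2 allows, nominal visit days, full attendance and assumed review times; slower enrolment widens the gaps. The resulting bias cannot be sized, because the protocol gives no figure for between-run variation. The primary safety outcomes and the antibody outcomes are untouched. The correction is worth making because it is cheap and cannot be made once runs have been done.

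**What to change.** In section 8.2.2.2, replace the timing condition. State that Elispot and ICS runs on cryopreserved PBMC begin only after all six timepoints from all four cohorts are stored (or recorded as missed), with samples randomised so that runs mix dosage groups and placebo. In section 8.2.3, state either that each of the two PBMC shipments is balanced by group or that runs start only after both have arrived. The whole blood assay, processed locally, needs no change for this purpose.

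The cost is two sentences, later cellular results and longer storage of the early samples. Against a start on day 140, runs would begin at the earliest 194 − 140 = 54 days later with no review time, 236 − 140 = 96 days later at 14 days, or 284 − 140 = 144 days later at 30 days. That is the same moment as the data point for the primary analysis in section 11.2, and the last cohort's Day 140 samples could not be assayed sooner in any case. Keeping all of one subject's timepoints in a single run is an optional layout; its absence is not an error.

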### **8.2.3 Specimen Preparation, Handling, and Shipping**

#### **Instructions for Specimen Preparation, Handling, and Storage**

Samples for Cellular Assays – All samples will be drawn into sodium heparin anticoagulant green top Vacutainer tubes. Tubes will be rocked several times immediately after drawing to ensure that blood does not form microclots. Each tube will be labeled with the study identifier, subject number, visit number and date, and processed within 2 hours. Of the 50 mL blood drawn, 30 mL will be used for PBMC isolation and cryopreservation and 10ml will be used for whole blood assays. Frozen samples will be shipped to Crucell/repository for analysis in IFN- $\gamma$  Elispot and Flow Cytometry. PBMC will be isolated from whole blood, cryopreserved at  $\leq -65^{\circ}\text{C}$  in a freezer,, and stored in a liquid nitrogen freezer in the vapor phase.

Samples for humoral immune assays – Of the 50 mL blood drawn, 10 mL will be used for humoral immune assays. Samples will be drawn into serum separator tubes. Following collection, blood will be allowed to sit between 30 and 60 minutes. Then it will be centrifuged in the Vacutainer tube according to the manufacturer's specifications. Under sterile conditions, the serum will be collected and aliquoted according to study procedures. Labeled aliquots will be placed in the appropriate fiberboard cryoboxes. The filled cryoboxes will be stored at  $\leq -65^{\circ}\text{C}$  in a freezer that is monitored.

**Specimen Shipment**

For analysis of the humoral response, two serum aliquots of each blood draw will be shipped to Crucell BV, Leiden, Netherlands and pending shipment failure, the remainder of the specimens will be stored at CNRFP. If additional storage is necessary, specimens may be shipped to Fishers Repository. For analysis of the cellular immune response, PBMC specimens will be shipped to Crucell BV, Leiden, Netherlands in two separate shipments. Whole blood assays will be processed at CNRFP/PDVAP laboratory in Ouagadougou, Burkina Faso.

## 9 ASSESSMENT OF SAFETY

### 9.1 Methods and Timing for Assessing, Recording, and Analyzing Safety Parameters

Safety will be assessed by frequency and incidence of AEs and SAEs in each dosage group. A safety monitoring committee (SMC) will be convened by DMID to review safety information from study subjects. See also section 9.4.

#### 9.1.1 Adverse Events, Reactogenicity, Serious Adverse Events

The investigator is responsible for reporting all AEs that are observed or reported during the study, regardless of their relationship to study product. Initial vaccine reactions will be assessed for at least 30 minutes after vaccination. Subjects will be visited by the study personnel to record both solicited vaccine reactions and any unsolicited AEs. Solicited local and systemic reactions and spontaneous AEs will be collected for 14 days following vaccination.

Solicited systemic reactions will include the following: headache, malaise, myalgia, fever, chills, nausea and vomiting. Solicited local injection site reactions will include the following: induration or swelling, erythema (redness), pain/tenderness, and ecchymosis or bruising.

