### **3.2 Study Outcome Measures**

#### **3.2.1 Primary Outcome Measure**

- The number of subjects experiencing severe (Grade 3) solicited injection site reactions within 14 days following vaccination.
- The number of subjects experiencing severe (Grade 3) solicited systemic reactions within 14 days following vaccination.
- The number of subjects spontaneously reporting severe (Grade 3) adverse events considered associated with the vaccination at any point during the study period.
- Serious adverse events considered associated with the vaccination reported at any point during the study period.

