## 9.2 Reporting Procedures

Solicited local and systemic reactions and spontaneously reported adverse events will be captured on the appropriate CRF.

Information to be collected for spontaneous AEs includes event description, date of onset, investigator assessment of severity, investigator assessment of relationship to study product, date of resolution of the event, seriousness, and outcome. The severity of non-serious AEs may be assessed by a licensed clinician (i.e., medical doctor, nurse practitioner, physician's assistant) listed on the Form FDA 1572. The causal relationship of non-serious AEs can be assessed by a licensed clinician (i.e. medical doctor, nurse practitioner, physician's assistant). All AEs occurring while on study will be documented appropriately regardless of relationship to the Study Vaccine. All AEs will be followed to adequate resolution.

Any medical condition that is present at screening will be considered as baseline and will not be reported as an AE. If the severity of any preexisting medical condition increases during the study period, then it will be recorded as an AE.

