If the SMC determines that it is safe to resume the study, but the subject who has already experienced events contributing to another halting rule experiences a SAE, severe AE or laboratory value that is considered by the investigators, ISM, and DMID Medical Monitor to be part of the original reported event, the study will not be halted for this event. If, however, such an event occurs and is considered by the investigators/ISM/DMID Medical Monitor/SMC to be unrelated to the prior event, the study will halt and formal SMC review will occur.

1. If 2 subjects in any single vaccine group experience severe (Grade 3) vaccination site pain/tenderness within 1 week following vaccination;
2. If 2 subjects in any single vaccine group experience moderate (Grade 2 or 3) fever that is associated with the vaccination within 1 week following vaccination;
3. If 2 subjects experience a spontaneously reported adverse event that is graded to be severe (Grade 3) or life-threatening and is associated with vaccination at any time during the follow-up period;
4. If 2 subjects experience a systemic solicited reactogenicity that is graded severe (Grade 3) (other than vaccine-related fever as defined above) within 14 days of vaccination.
5. If 1 subject experiences an SAE judged by an investigator to be associated with vaccination at any point during follow-up;
6. If 2 subjects develop a laboratory value that is considered severe (Grade 3) and that is judged to be associated with vaccination at any point during follow-up;
7. If 1 subject in any vaccine group tests positive for HIV;
8. Any report of new onset of neurologic symptoms. Any other observation occurs that, in the opinion of the PI or NIH/NIAID/DMID, results in a recommendation to halt enrollment and/or further vaccinations.

During clinic visit, the study personnel will ascertain that the reported severity of an AE by the subject meets the predefined criteria of the study of grading the severity of AEs.

If halting rules are triggered and the Internet is not available, then an immediate report will be made by phone and FAX.

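### Section 9.1.1 limits collection of spontaneous adverse events to 14 days after vaccination, which contradicts primary outcome 3, halting rule 3 and the protocol's own visit schedule to Day 365

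*Protocol*

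**What the plan says.** Section 9.1.1 sits under the Section 9.1 heading on methods and timing of safety assessment. Its first paragraph ends: "Solicited local and systemic reactions and spontaneous AEs will be collected for 14 days following vaccination". Spontaneous events are named expressly, so the sentence cannot be read as covering solicited reactions alone.

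Other parts of the protocol use a longer period:

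- **Section 3.2.1, third primary outcome:** "The number of subjects spontaneously reporting severe (Grade 3) adverse events considered associated with the vaccination at any point during the study period".
- **Section 9.3, halting rule 3:** two subjects with a spontaneously reported event "graded to be severe (Grade 3) or life-threatening and is associated with vaccination at any time during the follow-up period".
- **Section 9.2:** "All AEs occurring while on study will be documented appropriately regardless of relationship to the Study Vaccine".
- **Section 9.1.1, opening sentence of the same paragraph:** "The investigator is responsible for reporting all AEs that are observed or reported during the study, regardless of their relationship to study product".
- **Sections 7.3.1 to 7.3.21:** each of the 21 follow-up visits, the last at Day 365, includes assessment of spontaneous events since the previous visit.
- **Appendix A:** adverse event assessment is marked at every visit from Day 0 to Day 365.

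Two places point the other way for late follow-up. Section 11.2 describes follow-up after the primary data freeze as additional SAE surveillance. Inclusion criterion 7 describes the year of contact as being for serious adverse events.

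**The concern.** The protocol does not fix one collection period for non-serious spontaneous adverse events. A reader who combines the 14-day sentence with Section 11.2 and inclusion criterion 7 can arrive at a coherent scheme: all adverse events for 14 days after each dose, then SAEs only. That scheme cannot supply the data for primary outcome 3 or halting rule 3, both of which need non-serious Grade 3 associated events outside the 14-day windows.

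The groups are small. With 10 vaccinees per dosage group, one missed subject changes a group's observed rate by 1/10, or 10 percentage points. Halting rule 3 needs two subjects and, unlike rules 1 and 2, is not confined to a single vaccine group. One uncollected event in one cohort could therefore decide whether a review starts while another cohort is being vaccinated.

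**Working it through.** The plan gives no figure to reproduce. The check is a day count and a comparison of time windows.

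**Inputs.** Vaccinations fall on Days 0, 28 and 84 (Sections 7.2, 7.3.5, 7.3.11). The window is 14 days after each (Section 9.1.1). The last visit is Day 365 (Section 7.3.21). The primary analysis uses data through Day 140 of the last cohort (Section 11.2). Nominal visit days are used and visit windows are ignored.

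**Days covered if the sentence is followed literally.**

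- Windows: Days 0–14, 28–42 and 84–98, which is 15 + 15 + 15 = 45 days.
- Study days: Day 0 to Day 365 = 366. Coverage: 45/366 = 12.3%.
- Without the vaccination days: 3 × 14 = 42, and 42/365 = 11.5%.
- Uncovered: Days 15–27 (13), 43–83 (41) and 99–365 (267); 13 + 41 + 267 = 321, and 45 + 321 = 366.
- To Day 140: 45/141 = 31.9%. This applies to a subject followed to exactly Day 140. Earlier cohorts will have been followed longer by that cut, so their covered share is lower.
- Gaps before the third dose: 13 + 41 = 54 days, when further vaccination is still to come.

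**Visits outside every window.** Of the visit days in Appendix A, Days 56, 112, 140, 196, 252, 308 and 365 lie outside: seven visits, each with a spontaneous-event assessment required by Section 7.3.

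**Which outcomes and rules depend on the disputed sentence.**

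| Item | Period stated | Exposed? |
|---|---|---|
| Primary outcome 3 (spontaneous Grade 3, associated) | Study period | Yes |
| Primary outcome 4 (associated SAEs) | Study period | Largely not: separate SAE reporting in 9.2.1 |
| Halting rule 3 (spontaneous severe or life-threatening, associated) | Follow-up | Yes, for non-serious severe events |
| Halting rule 5 (associated SAE) | Follow-up | Largely not, for the same reason |
| Halting rule 6 (Grade 3 laboratory value, associated) | Follow-up | Not in this way: scheduled safety bloods are on Days 7, 35 and 91, all inside the windows |

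The conflict therefore bears on one primary outcome and one halting rule.

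**The case against.** The strongest reply is that context narrows the sentence. The sentence just before it describes study personnel visiting subjects to record solicited and unsolicited events. Section 7.2 and footnote 5 of Appendix A set the home visits at the 14 days after each dose, so the disputed sentence may simply describe home collection. For field workers a 14-day instruction would then lose nothing, because later events are taken at clinic visits. The recall period runs from one visit to the next, so Section 7.3 leaves no gap, and Section 7.5 also asks for adverse events at early termination.

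Much of this stands. It shows that the procedures for full collection exist and that the fault lies in one sentence. It does not remove the conflict. The sentence speaks of collection without mentioning home visits, it stands in the section that sets safety timing, and the SAE-only wording in Section 11.2 and inclusion criterion 7 supports the literal reading.

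The number of events at risk may also be small. Section 9.1.1 calls an event associated only if it is temporally related to the product and no other cause explains it. Loss need not be proportional to uncovered days.

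A reader might go further and infer that outcome 3 is under-counted by design, with 321 of 366 days (88%) lacking any spontaneous-event collection. The documents do not support that: it would require staff to disregard Section 7.3, Section 9.2 and Appendix A. Nor do they support the inference that late laboratory events under rule 6 would be lost because of this sentence, or that SAEs would go unreported.

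**Conclusion.** The inconsistency is real and needs correction: the 14-day limit on spontaneous adverse events in Section 9.1.1 is incompatible with primary outcome 3 and halting rule 3. Coverage of 12% of follow-up, or 32% to Day 140, is the worst case under literal adherence and measures days, not lost events. What is at risk is ascertainment of late, non-serious Grade 3 associated events. How much would be lost depends on how the case report form and site instructions interpret the sentence. Neither is available here, so no expected number of missed events can be given.

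**What to change.** In Section 9.1.1, restrict the 14-day window to solicited local and systemic reactions and to the daily home visits. Add one sentence that states a single collection period for spontaneous adverse events, serious and non-serious, consistent with Sections 3.2.1, 7.3, 9.2 and 9.3. Reconcile Section 11.2 and inclusion criterion 7 with it, so that the SAE-only description of late follow-up does not contradict the stated period. Check the case report form and the Manual of Procedures against the revised text.

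The cost is a few sentences of protocol text. No visit, blood draw or assessment is added, because adverse event assessment is already scheduled at every visit to Day 365.
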